### Monitoring

#### Data safety monitoring

Completeness of data collection will be assessed when 20% of the sample completes treatment, and improvements will be made, if necessary. Treatment completion rates and rates of the incidence of serious adverse events (SAE) will be evaluated at the end of treatment for 20% and 40% of the sample, respectively.

#### Safety monitoring

In the event of an SAE occurring at any institution, the contents shall be promptly reported to the Institutional Review Board (IRB) of the leading and corresponding institutions using the prescribed form. If no SAEs occur, monitoring results will be included in the final report. Any protocol violations, non-compliance, or unexpected problems will also be reported to the IRB of the leading and corresponding institutes. If more than five SAE are reported at any institution, the principal investigator, along with the co-investigators, will discuss the study’s sustainability and the need to potentially discontinue or modify the study. The results of this discussion will be reported to the IRB. In the event of participants experiencing physical damage as a result of participating in this study, the principal investigator shall provide compensation in accordance with the provisions of relevant laws and regulations.

#### Auditing

The ACROSS team will monitor data collection and protocol adherence. Auditing of investigators will be conducted at least annually and may be conducted at additional times, if necessary.

### Statistical analysis

#### Sample size calculation

Based on previous research [11], it is anticipated that the experimental group receiving mFOLFIRINOX as adjuvant treatment will achieve a 3-year DFS rate of 77.5%, with an improvement of 12.5% compared to the control group, which is estimated to have a 65% DFS rate. To determine the sample size for the study, a power analysis was performed using the PASS (Power Analysis and Sample Size) 13.0 program (NCSS, LLC, Kaysville, Utah, USA). The calculations indicated that a minimum of 156 subjects will be required for each treatment arm, considering the desired statistical power of 80%, the significance level of 10%, and the dropout rate of 10%. Therefore, a total of 312 subjects, equally stratified and randomized, will be enrolled to ensure adequate statistical power and robust results.

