## Background

Based on numerous studies conducted since the publication of the MOSAIC trial in 2004 [1–3], the standard adjuvant treatment for stage III colon cancer (CC) following radical resection has evolved to involve doublet therapy consisting of oxaliplatin and 5-fluoropyromidine (5-FU). The addition of irinotecan to 5-FU for the treatment of radically resected stage III CC did not demonstrate improved survival compared to that achieved with 5-FU alone [4–6]; additionally, the combination of targeted agents, such as cetuximab or bevacizumab, with chemotherapy also failed to demonstrate remarkable oncological benefits [7–10]. Consequently, most international guidelines recommended a 6-month regimen of FOLFOX (oxaliplatin and 5-FU) or CAPOX (oxaliplatin and capecitabine) for adjuvant treatment of stage III CC.

Recently, the findings of the IDEA collaboration study [11] highlighted equivalent disease-free survival (DFS) rates with 3 months of CAPOX and with 6 months of CAPOX and substantially reduced toxicity with the former. Consequently, the National Comprehensive Cancer Network guidelines currently suggest 3 months of CAPOX or 3 or 6 months of FOLFOX as options for treatment of low-risk stage III (pT1-3N1) CC and 3–6 months of CAPOX or 6 months of FOLFOX for high-risk stage III (pT4N1-2 or TanyN2) CC treatment.

However, a paucity of information remains for patients with high-risk stage III CC, and research exploring more extensive adjuvant treatment options is scarce. According to the current guidelines, 3 months of CAPOX should be considered the first option for all high-risk stage II CC, low-risk stage III CC, and high-risk stage III CC. However, these patient groups exhibit considerably different prognoses. The IDEA study reported a 3-year DFS rate of 62.7–64% for patients with high-risk stage III CC compared to the 83.1–83.3% rate for patients with low-risk stage III CC [11]. Consequently, there is a need for research on more extensive adjuvant treatments for patients with high-risk stage III CC, even after successful R0 resection.

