Personalized medicine is a crucial concept in the current treatment paradigm for metastatic colorectal cancer, and its extension to the management of non-metastatic colorectal cancer, particularly high-risk stage III CC, which carries high potential of progression to metastatic disease, is warranted. Therefore, it is essential to evaluate whether the triplet regimen of mFOLFIRINOX (oxaliplatin, irinotecan, and 5-FU), which has recently demonstrated superior efficacy in patients with unresectable metastatic colorectal cancer, can improve the prognosis of patients with high-risk stage 3 CC. Although a prospective single-arm study with a small sample size reported the safety and efficacy of triplet chemotherapy for locally advanced, resectable CC [12], and a randomized prospective study regarding a conventional regimen of triplet chemotherapy as an adjuvant treatment for high-risk stage III CC has been initiated in overseas [13], randomized controlled trials investigating the modified regimen of mFOLFIRINOX are lacking.

Therefore, the goal of this study is to evaluate the oncologic efficacy and safety of mFOLFIRINOX in comparison to those of the current standard of care, mFOLFOX 6, as an adjuvant treatment for patients diagnosed with high-risk stage III colon cancer after radical resection.

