## Methods

### Study design

This multicenter, randomized (1:1), open-label, phase II trial assesses the effectiveness and toxicity of mFOLFIRINOX compared to those of mFOLFOX-6 as an adjuvant treatment for patients with high-risk stage III CC. Patient enrollment will be performed across 11 tertiary hospitals in one country. The flow-diagram of the study is presented in Fig. 1.

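### Both design rates are credited to reference [11], but the Background's account of it gives 62.7–64% for control and no triplet arm; on a two-proportion test, 156 per arm follows from 64%, not the printed 65%

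*Protocol article*

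**What the plan says.** The Sample size calculation section opens its derivation with "Based on previous research [11], it is anticipated that the experimental group receiving mFOLFIRINOX as adjuvant treatment will achieve a 3-year DFS rate of 77.5" per cent and continues in the same sentence "with an improvement of 12.5% compared to the control group, which is estimated to have a 65% DFS rate". The other inputs are "considering the desired statistical power of 80%, the significance level of 10%, and the dropout rate of 10" per cent. Sidedness and test are not named. The result is 156 per arm, 312 in total.

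The Background says of the same reference: "The IDEA study reported a 3-year DFS rate of 62.7–64% for patients with high-risk stage III CC". It describes the study as one that "highlighted equivalent disease-free survival (DFS) rates with 3 months of CAPOX and with 6 months of CAPOX". No triplet arm is mentioned.

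On triplet therapy, the Background mentions a small single-arm study without giving a DFS rate, and adds that "randomized controlled trials investigating the modified regimen of mFOLFIRINOX are lacking".

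**The concern.** There are two separate faults, and both can be checked inside the document.

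1. **Attribution.** The 77.5% for mFOLFIRINOX is introduced as resting on a study that, as the protocol describes it, compared durations of a doublet. No section gives a source for 77.5% or a reason for choosing 12.5 points.
2. **Control rate.** For the same kind of patient and the same reference, one section gives 62.7–64% and another uses 65%. The planning value is 1.0 to 2.3 points above the protocol's own range, without explanation.

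These two rates determine the sample size. If the rates entered in the software differ from the printed ones, then the printed difference, the printed power, or both do not describe this trial.

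**Working it through.** **Inputs.** From Sample size calculation: control 65%, experimental 77.5%, power 80%, significance level 10%, dropout 10%, 156 per arm. From Study design: 1:1 allocation. From Background: 62.7–64%. Assumed, because the article does not say: a pooled two-proportion test without continuity correction, with sidedness tried both ways.

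**Formula.** With p̄ the mean of the two rates and d their difference,

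n per arm = [z_α √(2p̄(1−p̄)) + z_β √(p₁(1−p₁)+p₂(1−p₂))]² / d²,

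with z_α = 1.645 (two-sided 10%) or 1.282 (one-sided 10%) and z_β = 0.842. Round up, divide by 0.90, and round up again.

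**Step 1: the plan's own figure from the printed rates.** For 65% v 77.5%, p̄ = 0.7125 and d = 0.125. The two square roots are 0.6401 and 0.6339.
- Two-sided: (1.645×0.6401 + 0.842×0.6339)² / 0.015625 = 161.1, so 162 evaluable; 162/0.9 = 180.
- One-sided: 117.3, so 118 evaluable; 118/0.9 gives 132.

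Neither is 156. Other forms, after dropout (two-sided / one-sided): continuity-corrected 197 / 148, unpooled 178 / 129, arcsine 179 / 130.

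**Step 2: the control rate from the Background.** For 64% v 77.5%, p̄ = 0.7075 and d = 0.135. The square roots are 0.6433 and 0.6362. Two-sided: 139.4, so 140 evaluable; 140/0.9 = 155.6, so **156**, the stated figure.

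| Rates (two-sided 10%) | Difference | Evaluable per arm | After 10% dropout | Power with 140 evaluable |
|---|---|---|---|---|
| 65 v 77.5 (printed) | 12.5 | 162 | 180 | 74.9% |
| 64 v 77.5 | 13.5 | 140 | 156 | 80.2% |
| 62.7 v 77.5 | 14.8 | 118 | 132 | 85.9% |
| 64 v 76.5 | 12.5 | 165 | 184 | 74.2% |
| 62.7 v 75.2 | 12.5 | 169 | 188 | 73.3% |

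**Step 3: what 312 patients deliver.** 156 × 0.9 = 140.4, so 140 evaluable per arm. Power is Φ[(d√140 − z_α √(2p̄(1−p̄))) / √(p₁(1−p₁)+p₂(1−p₂))]. At the printed rates, two-sided, this is Φ[(1.479 − 1.053)/0.634] = Φ(0.672) = 74.9%; one-sided it is 85.1%. Solving the same expression for 80% two-sided power gives a detectable difference of 13.3 points from a 65% control rate, 13.5 from 64% and 13.6 from 62.7%.

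**Step 4: can a log-rank calculation explain 156?** The hazard ratio is ln(0.775)/ln(0.65) = 0.592. Events (Schoenfeld, two-sided) = 4(1.645+0.842)²/(ln 0.592)² = 89.8, so 90. If every patient is followed for exactly 3 years, the mean event probability is 0.2875. That gives 90/0.2875 = 313 patients, or 157 per arm **before** dropout and 175 after it. So about 156 appears if the dropout allowance was left out. It also appears with dropout if follow-up is longer for some patients: 1 year of accrual plus 3 of follow-up gives 155, and 3 plus 2 gives 156. The article states no timing for the calculation.

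**The case against.** **The 65% is labelled an estimate.** A planning value one point above a cited range may be rounding, or a figure for patients on a regimen closer to the control arm. The study itself is not at hand. This stands: a reader might infer that 65% contradicts the source, but the documents support only that it differs from the protocol's own report of that source, unexplained.

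**A target need not have been observed.** For an untested regimen the experimental rate is a hypothesis, and the sentence can be read as a control anchor plus a chosen gain. That defends 12.5 points as a target. It does not defend wording that places the triplet rate under reference [11].

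**The control rate may hardly matter.** If 12.5 points is kept, moving to 62.7–64% raises the requirement only from 180 to 184–188 per arm. If 77.5% is kept, a lower control rate raises power. Both are true, so the printed rate is not simply too favourable. The difference matters because it decides whether 156 follows from the stated inputs.

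**Other temptations.** A reader might infer that the Background's negative results for irinotecan added to 5-FU, or for targeted agents, count against the assumed gain. Neither is the triplet, and the Background also gives a rationale for it from metastatic disease. Nor does the article say that a non-significant result would be taken as no benefit.

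**Conclusion.** The point holds in limited form. Reference [11], as the protocol describes it, cannot support 77.5%, and the 65% control rate is not reconciled with the 62.7–64% given elsewhere in the same article.

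The size, on a two-sided 10% two-proportion test with 10% dropout: the printed rates need 180 per arm against 156 enrolled, and 140 evaluable per arm give about 75% power where 80% is stated.

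The exact match at 64% v 77.5% makes it tempting to conclude that 64% was entered and that the true design difference is 13.5 points. The documents do not prove this, because the log-rank routes in step 4 also reach about 156 from the printed rates. Nor do they show that the trial is underpowered: if the 10% level is one-sided, the printed rates need only 132 per arm and the power with 140 evaluable is 85.1%. What is established is that the printed inputs do not determine the printed sample size, and that one of them disagrees with the Background.

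**What to change.** In Sample size calculation:

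1. Reconcile the control rate with the Background: use one value from 62.7–64%, or keep 65% and say why it differs.
2. State the two rates, the sidedness and the test actually entered in the software and, if it was a log-rank calculation, the accrual and follow-up times.
3. Restate the power, or the detectable difference, that 312 patients deliver after 10% dropout.
4. Cite reference [11] for the control rate only, and call the gain the target difference the trial is designed to detect.

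The cost is a few sentences and one re-run of the power calculation, with no added patients. The downside is that the stated power or detectable gain may become less favourable: on the two-sided two-proportion test, about 75% for 12.5 points from 65%, or 80% only for a gain of about 13.3 to 13.6 points.

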### Endpoints

#### Primary endpoint

The primary endpoint of the study is the 3-year DFS rate based on intention-to-treat analysis, which is defined as the proportion of patients who were alive without recurrence at 3 years from the date of surgery. It will be calculated using the time from the date of surgery to the date of recurrence detection, death, or the last follow-up. In cases where patients are lost before the 3-year mark, their data will be censored as of the last follow-up date and assessed accordingly.

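### The stated 156 per arm does not correspond to 80% power for the 3-year DFS rate with 10% dropout, whether the 10% level is one-sided or two-sided

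*Protocol article*

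**What the plan says.** The Sample size calculation section of the protocol article expects that the mFOLFIRINOX arm "will achieve a 3-year DFS rate of 77.5%, with an improvement of 12.5% compared to the control group"; it puts the control rate at 65%. It then states that at least "156 subjects will be required for each treatment arm, considering the desired statistical power of 80%, the significance level of 10%, and the dropout rate", which is put at 10%, giving 312 in total. PASS 13.0 is named as the software. The section names no test, does not say whether the 10% is one-sided or two-sided, and gives no accrual or follow-up period for the calculation.

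The Primary endpoint section defines the 3-year DFS rate as "the proportion of patients who were alive without recurrence at 3 years from the date of surgery", analysed by intention to treat. The rate is calculated from time to recurrence, death or last follow-up, and patients lost before 3 years are censored at last follow-up.

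The Background section gives the range behind the control rate: "The IDEA study reported a 3-year DFS rate of 62.7–64% for patients with high-risk stage III CC". The sample size section cites the same study.

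**The concern.** The article gives both rates, the power, the significance level, the dropout and the resulting size, so the calculation can be checked against the declared endpoint. It fails in opposite directions according to sidedness: 156 is too few for a two-sided 10% test and more than the minimum for a one-sided one. The stated 80% is therefore not the power of a comparison of 3-year rates under either reading.

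This paragraph is the only quantitative justification for 312 patients. A negative result would be judged against the 80%. The sidedness moves the true power by about 10 percentage points and also decides what counts as a positive result.

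**Working it through.** **Inputs (Sample size calculation).** p1 = 0.65, p2 = 0.775, difference d = 0.125, mean rate 0.7125, power 80% (z = 0.842), dropout 10%, allocation 1:1. The 10% level gives z = 1.645 two-sided or 1.282 one-sided.

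**1. Size for a comparison of two 3-year rates (pooled normal formula).**

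n = [z_a × √(2 × 0.7125 × 0.2875) + z_b × √(0.65 × 0.35 + 0.775 × 0.225)]² / d²

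The two square roots are √0.4097 = 0.6401 and √0.4019 = 0.6339.

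- Two-sided: (1.645 × 0.6401 + 0.842 × 0.6339)² / 0.125² = 161.06, so 162 evaluable. With dropout: 161.06/0.9 = 178.95, or 162/0.9 = 180. That is 179-180 enrolled per arm.
- One-sided: (1.282 × 0.6401 + 0.842 × 0.6339)² / 0.125² = 117.3, so 118 evaluable. With dropout: 117.3/0.9 = 130.3, or 118/0.9 = 131.1. That is 131-132 enrolled per arm.

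Other standard versions with dropout, two-sided and one-sided: unpooled 178 and 129; arcsine 179 and 130; continuity-corrected 197 and 148. None gives 156; the nearest is the one-sided continuity-corrected 148.

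**2. Size when losses are censored, as the endpoint section says.** Assume constant hazards and exponential loss reaching 10% by 3 years. A Kaplan-Meier comparison at 3 years with Greenwood variance then needs about 168 enrolled per arm two-sided or about 123 one-sided. Again neither is 156.

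**3. Power of 156 enrolled per arm.**

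| Analysis of the 3-year rate | Two-sided 10% | One-sided 10% |
|---|---|---|
| Dropouts contribute nothing (156 × 0.9 ≈ 140 per arm) | 75% | 85% |
| Kaplan-Meier at 3 years, 10% loss censored | 77% | 87% |
| No dropout at all (156 per arm) | 78.9% | 87.9% |

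**4. Can 156 be reproduced another way?** Under proportional hazards the hazard ratio is ln(0.775)/ln(0.65) = 0.592, and its logarithm is -0.525. Two-sided Schoenfeld events are 4 × (1.645 + 0.842)² / 0.525² = 89.8. With everyone followed for exactly 3 years, the mean event probability is (0.35 + 0.225)/2 = 0.2875.

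- No dropout: 89.8/(2 × 0.2875) = 156.2 per arm, which matches. With dropout: 156.2/0.9 = 173.5.
- With accrual and follow-up periods that the article does not give, other two-sided Schoenfeld designs come near 156 with the dropout allowance included. Three years of accrual plus 2 of follow-up needs about 139 before dropout and 155 after; 4 plus 1.5 years gives about 156 after dropout.

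The figure therefore has several possible origins, and the article does not allow a choice between them.

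**5. Control rate.** With 62.7-64% and the same 12.5-point gain, 140 per arm gives 73-74% two-sided, against 75% at a control rate of 65%. This effect is minor.

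**The case against.** The strongest reply is that the test is not named, so a log-rank design cannot be excluded. DFS is recorded as time to event, and 3-year rates are commonly converted to a hazard ratio for planning. If a log-rank test used all follow-up, about 140 effective patients per arm would give roughly 87% two-sided power with 3 years of accrual plus 3 of follow-up, and about 90% with 5 plus 3. These are assumed periods and constant hazards, but on that reading there is no deficit. The test and its inputs may also be set out in the full protocol, which is not shown. This reply stands to the extent that the trial cannot be called underpowered outright, and the absence of these details from an article is not a fault in itself. It does not rescue the sentence as written. A log-rank test compares whole curves, whereas the declared endpoint is the rate at 3 years, and for that rate the stated inputs and result disagree.

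Two stronger readings are tempting. A reader might infer that the trial falls short of 80% power; that holds only if the 10% is two-sided, which the article does not say. A reader might also infer from the 156.2 match that dropout was left out. The article says that dropout was considered, and designs that include it come equally close, so the match is not evidence of an omission.

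It is also fair to say that 75% is pessimistic. It treats patients who drop out as carrying no information, whereas the plan censors them; about 77% is nearer to the described analysis. Setting the control rate one point above the cited range is a planning judgement, not an arithmetic error.

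**Conclusion.** The stated size and the stated power do not match for the primary endpoint as defined. Two-sided, 80% power needs 179-180 enrolled per arm, and 156 delivers about 75-77%. One-sided, 131-132 would be enough, and 156 delivers about 85-87%.

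These figures rest on 65% against 77.5%, 10% dropout and normal approximations. The upper end of each power range also assumes constant hazards and loss spread exponentially over 3 years. The direction of the mismatch depends on a sidedness that the article does not state, and the origin of 156 stays undetermined.

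**What to change.** Keep 312 patients and amend the sample size paragraph.

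- State whether the 10% is one-sided or two-sided, and name a primary test that matches the endpoint. For the 3-year rate as defined, this would be a comparison of Kaplan-Meier estimates at 3 years with losses censored.
- Replace the 80% with the power that 312 patients and 10% loss deliver for that test: about 75-77% two-sided or about 85-87% one-sided. Say how dropout entered the calculation. A line for control rates of 62.7-64% would be a useful addition.
- If 156 came from a log-rank design, state its accrual and follow-up periods and the event target (about 90 DFS events for 80% power at two-sided 10%). Make that log-rank test the primary analysis and report the 3-year rates as its summary.

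The cost is a rewording by amendment and, if the test is two-sided, a slightly less favourable stated power. No extra patients are needed. The sidedness and the test should be settled before outcomes are compared by arm. The Trial status section reports only 19 patients enrolled by July 2023.

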#### Outcome assumptions

Statistical analyses for primary and secondary outcomes of the intent-to-treat group and per-protocol group will be performed using SPSS version 26 (IBM, Armonk, NY, USA).

### Analysis of prognostic factors and biomarkers

Prognostic factors and biomarkers will be analyzed in this study. Information about various clinical, pathological, and molecular characteristics, including microsatellite instability, KRAS, NRAS, BRAF, and HER2 status, of the enrolled patients will be collected and assessed. The analysis of these factors will provide valuable insights into the prognosis and potential treatment response of patients with high-risk stage III CC. Through these analyses, we will identify molecular markers that might affect disease progression and treatment outcomes. This comprehensive analysis of prognostic factors and biomarkers will enhance our understanding of the underlying biology of high-risk stage III CC and could reveal important associations between these molecular characteristics and clinical outcomes, thereby guiding personalized treatment and optimized patient management.

## Discussion

Despite their poor outcomes, there is a considerable lack of research regarding the prognosis and treatment outcomes of patients diagnosed with high-risk stage III CC. Although triplet chemotherapy holds theoretical promise for providing more intensive systemic control in this patient population, its safety and oncological superiority need to be established through prospective randomized controlled studies.

The conventional triplet chemotherapy regimen (oxaliplatin 85 mg/m^2^, irinotecan 180 mg/m^2^, and 5-FU 2400 mg/m^2^) is associated with considerably higher toxicity than is the modified regimen (oxaliplatin 85 mg/m^2^, irinotecan 150 mg/m^2^, and 5-FU 2400 mg/m^2^). Therefore, the conventional regimen may not be suitable for Asian patients, as it may potentially result in poor oncological outcomes because of decreased rate of completion of the planned treatment schedule, reduced drug dose, and poor compliance [14].

The goal of this study is to assess the effectiveness and toxicity of mFOLFIRINOX and mFOLFOX 6 in 312 patients who have been diagnosed with high-risk stage III CC after radical resection.

We expect that our findings will help elucidate the oncologic efficacy and safety of adjuvant triplet chemotherapy for patients with high-risk stage III CC and provide useful information regarding this treatment. Ultimately, the findings of this study will improve the prognosis and refine personalized treatment approaches for patients with high-risk stage III CC.

